Current first-line ITP treatment is with high-dose corticosteroids but this has several downsides. First, the majority of patients suffer significant side effects including mood swings, difficulty sleeping, weight gain, high blood pressure, diabetes, gastric irritation, skin thinning and osteoporosis. A published survey of patients with ITP reported 98% had at least one side effect and 38% stopped or reduced dosage due to intolerable side effects.^8^ In the UK ITP registry, the most frequently reported comorbidities were related to corticosteroids and correlated with duration of treatment (hypertension in 30%, diabetes in 19%).^9^ The second problem is that patients are heterogeneous in their response to corticosteroid with some (approximately 20%) not responding at all and the majority of others (70%–90%) relapsing when the corticosteroids are reduced or stopped.^7 10 11^Patients, who are refractory or relapse (the majority), remain at risk of bleeding/bruising, which occasionally can be severe including intracranial haemorrhage.^12^ They often receive more corticosteroid with associated side effects. Some require hospital admission and expensive rescue therapies (eg, intravenous immunoglobulin, Ig for a 70 kg patient=£3906). They continue to require frequent blood tests and doctor visits and are usually unable to continue their normal activities until their illness is controlled. Fatigue is also associated with disease activity and can be severe.^13^ Physical factors combine with psychological stress through fear of bleeding, need for time off work and lifestyle restrictions due to bleeding risk to adversely impact quality of life.^14 15^

First-line treatment for ITP is unsatisfactory but it remains unchanged for decades. Although a small number of studies have tested alternative approaches, a well-tolerated, effective and durable new approach has not been conclusively demonstrated. High-dose corticosteroid remains the standard first-line treatment recommended in most countries.^10^

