### Primary outcome

Time from randomisation to treatment failure defined as a platelet count <30×10^9^/L and a need to commence second-line treatment. This will include patients who are refractory (platelet count <30×10^9^/L in spite of 2 weeks treatment in the steroid arm or platelet count <30×10^9^/L in spite of 2 months treatment in the steroid +MMF arm) or who initially respond but then relapse (defined clinically as platelet count <30×10^9^/L and need for further therapy). Patients with a clinical need to start second-line treatment early (within 2 weeks for the steroid only arm and within 2 months for the MMF and steroid arm), for example, due to significant bleeding, will also be classed as treatment failures.

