### Statistical analysis

The full statistical analysis will be written into a statistical analysis plan available separately. The analysis will produce a Consolidated Standards of Reporting Trials diagram for the reporting of clinical trials.

The baseline characteristics of the two groups will be tabulated but not tested for statistically significant differences between the groups.

The primary analysis is by intention to treat. However, an investigation of compliance with the treatment pathway and compliance with the criteria for changing to a second-line therapy will be carried out prior to the primary analysis to check the date of the primary event. The primary event is the date at which there was a requirement for second-line therapy. Where the platelet count falls below the level required for this treatment decision, the first date at which either symptoms or a blood test revealing this event will be used. If a clinician decides to use a second-line therapy without a platelet count below the criteria, the date of the treatment decision/new prescription will be taken to represent that event. The results will be expressed as an HR with 95% CI, median time to event if more than 50% have had an event and plotted as Kaplan-Meier curves.

The primary analysis will contain all patients who are randomised for as long as they have been followed up or until their first event in a survival analysis using intention to treat methodology. All patients will be followed up to 12 months. In addition, patients who have not had an event in the first 12 months postrandomisation will be followed until their first event or until the last patient has reached the 12-month point—whichever is the sooner and included in the analysis until that time accordingly. Sensitivity analyses will include landmark analysis or shifting the time line to classify all treatment failures before 2 months as at 2 months in order to prevent potential biases caused by different definitions of treatment failure time frames between the two groups.

Analysis of other outcomes will use as full a data set as possible and focus on the 12-month data point or area under the curve as appropriate and detailed in the analysis plan.

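### Refractory failure is declared after 2 weeks in the steroid arm but after 2 months in the steroid+MMF arm, which biases the primary HR towards MMF; the plan corrects this only in sensitivity analyses, and only in part.

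*Protocol article*

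**What the plan says.** The Primary outcome section of the protocol article defines treatment failure as a platelet count below 30×10^9/L together with a need for second-line treatment. Three routes lead there:

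- **Refractory disease**, with arm-specific windows: a low count "in spite of 2 weeks treatment in the steroid arm or platelet count <30×10^9^/L in spite of 2 months treatment" in the arm that adds MMF.
- **Relapse after response**, defined in the same way in both arms.
- **Early need**: the clause opens "Patients with a clinical need to start second-line treatment early (within 2 weeks for the steroid only arm and within 2 months for the MMF"; it goes on to class these patients as failures too.

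The Statistical analysis section states "The primary analysis is by intention to treat" and keeps this endpoint as primary. For dating a low-count event, "the first date at which either symptoms or a blood test revealing this event will be used". It then plans a correction: "Sensitivity analyses will include landmark analysis or shifting the time line to classify all treatment failures before 2 months as at 2 months", with the reason given as "in order to prevent potential biases caused by different definitions of treatment failure time frames between the two groups". The Introduction describes steroid-treated patients as heterogeneous, "some (approximately 20%) not responding at all".

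**The concern.** Both arms take the same steroid course, so the two windows are a difference in measurement added to the difference in treatment. Two mechanisms follow.

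1. **Timing.** A refractory patient can fail at about 0.5 months on steroid alone and at about 2 months on steroid+MMF.
2. **Classification.** A patient who is low at 2 weeks and recovers by 2 months can be a failure on steroid alone and never one on steroid+MMF.

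Both favour the experimental arm, and the primary HR cannot separate either from a drug effect. The trial is open label and the need for second-line therapy is a clinical judgement, so the longer window may also affect when that need is declared. The protocol sees the problem but leaves the headline result on the arm-specific rule.

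**Working it through.** **Inputs from the protocol article.** 60 patients per arm; control median 5.0 months, with 70% failed by 12 months; target median 10 months; accrual over 12 months and follow-up until the last patient reaches 12 months, so 12 to 24 months each; loss below 5% (Sample size calculation). About 20% steroid non-response (Introduction). Windows of 2 weeks (0.5 months) and 2 months (Primary outcome).

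**Assumed, not in the document.** Two-sided 5% level; 5% loss per year; the share of patients low at 2 weeks who recover by 2 months under the same care (late recovery, 0% to 50%); the share of refractory MMF-arm patients switched early (none or half).

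**Step 1: reproduce the stated power.** With exponential survival, hazards are ln2/5 = 0.1386 and ln2/10 = 0.0693 per month. With loss, 94.2 events are expected. The test of the log hazard ratio, with variance 1/d1 + 1/d2, gives 91.55%, against 91.5% stated. The design inputs are therefore read correctly.

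**Step 2: the patients concerned.** 20% of 60 is 12 per arm. In the steroid arm, all 12 fail at about 0.5 months if each also needs second-line therapy. In the MMF arm without early switching, 12, 9 or 6 fail at about 2 months for 0%, 25% or 50% late recovery; the others stay event-free until they relapse.

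**Step 3: simulate an inert MMF.** The responders' relapse rate is set so that the whole control arm has a median of 5 months. With a constant hazard this is −ln(0.5/0.8)/(5 − 0.5) = 0.470/4.5 = 0.104 per month. A Weibull version (shape 0.84) that also meets 70% failed at 12 months gives similar answers. The ranges below span the model versions (2,500 to 4,000 trials per scenario).

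| Late recovery | Primary HR | False wins for MMF | Primary HR, half switched early | Shifted HR | Landmark HR at 2 months |
|---|---|---|---|---|---|
| 0% | about 0.93 | 4–5% | about 0.98 | 0.98–0.99 | 1.34 |
| 25% | 0.89 | 8–9% | about 0.95 | 0.93 | 1.24 |
| 50% | about 0.84 | 12–14% | about 0.92 | 0.87–0.88 | 1.15 |

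Nominal false wins are 2.5%. With half switched early they are about 3–7%. With the shift they are 2.7%, 6.2% and 10.1%.

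**Step 4: confirm the cause.** When refractory patients in both arms are declared at 2 weeks, the HR is 1.00 and false wins are 2.6%. The window is the source.

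**Step 5: the planned corrections.** The shift moves dates and reclassifies nobody, so it works at 0% late recovery and leaves a residue above that. A landmark at 2 months removes steroid-arm refractory patients who have already failed, while their MMF-arm counterparts fail just afterwards; the HR then exceeds 1, with 25% (0% late recovery) to 9% (50%) false results against MMF. A landmark placed after the MMF decision gives an HR near 1.00 here, but it ignores every early failure and compares groups selected after randomisation.

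**Step 6: the event-date rule.** If the Statistical analysis section means that an MMF-arm refractory failure is back-dated to its first low count, the HR is 1.00, 0.93 and 0.86 for 0%, 25% and 50% late recovery, with false wins of 2.0%, 6.2% and 11.7%. The article does not say whether this is intended.

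**The case against.** The case for the plan has substance. The document gives a reason for the longer window: MMF may take up to 2 months to work. The aim is to compare two pathways. The bias is disclosed, and the list of sensitivity analyses is open. Several limits on the size stand:

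- **A low count alone is not an event.** A reader might infer that every steroid-arm patient below 30×10^9/L at 2 weeks has failed. The definition also asks for a need for second-line therapy, so failing the whole 20% at that point is an upper-end assumption.
- **MMF-arm patients need not wait 2 months.** The early-need clause counts those who require second-line therapy sooner. With half switched early, the bias falls by roughly half or more.
- **Late recovery is unsourced.** It also sits uneasily with the Introduction's description of the 20%, which suggests no response at all. At 0%, the shift nearly removes the bias, and back-dating does so too.
- **Not every failure before 2 months is affected.** The control figures imply that 24% (constant hazard: 1 − exp(−0.1386 × 2)) to 32% (a curve through both control points) fail by then. A reader might take all of these as patients for whom the rules differ. Early relapses are among them, and relapse has one definition. For the same reason, the documents do not support a scenario in which MMF-arm relapses wait until 2 months.

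The slow onset explains the rule but does not make the comparison even. Early switching and back-dating cannot be assumed: one rests on open-label judgement, the other on an ambiguous sentence.

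**Conclusion.** The concern holds. The arm-specific window biases the primary HR towards MMF, through timing and through classification. With 20% refractory and no early switching, the null HR is about 0.93 to 0.84 and one-sided error is about 4–5% to 12–14% instead of 2.5%, as assumed late recovery goes from 0% to 50%. With half of refractory MMF-arm patients switched early, the HR is about 0.92 to 0.98 and the error about 3–7%. With back-dating and no late recovery, the bias nearly vanishes. The direction is secure; the size depends on shares that the document does not give.

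A reader might infer that the definition by itself could deliver a positive trial. The figures do not support that. With about 94 events, significance needs an observed HR near exp(−1.96 × 2/√94.2) = 0.67, so chance must add a good deal to a null HR of 0.84 to 0.93, and the design HR is 0.5. What the rule does is raise the chance of a false win and exaggerate a true effect.

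The planned sensitivity analyses do not settle the matter: the shift mends timing only, and the landmark can reverse the bias.

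**What to change.** - **Primary analysis.** Use one failure clock in both arms. As a minimum, promote the plan's own shifted analysis, in which every failure before 2 months in either arm is dated at 2 months, and move the arm-specific rule to sensitivity.
- **Classification.** The shift does not equalise who counts, so add a sensitivity analysis that applies one common definition to the recorded platelet counts and second-line start dates of both arms. Use a visit window, because counts are routine and range from weekly to monthly or less often (Data collection).
- **Landmark.** Keep it as description if wanted, not as the correction for this bias.
- **Event date.** Reconcile the dating rule under Statistical analysis with the windows under Primary outcome, and state how a patient whose count is low from the start is dated in each arm.

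The cost is wording in the protocol and SAP; the counts and treatment data are already collected. The downside is lost information on timing within the first 2 months, and slight dilution of a true effect where a common early criterion counts patients before MMF has had its stated onset time. The change concerns the analysis endpoint only, not when any patient is treated.

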### Secondary outcomes

Medication side effects, toxicity or other adverse events (including infection episodes).Bleeding events.Site and type of bleeding.Treatment required for bleeding.Whether hospital admission was required.Whether ITP rescue treatments were needed.Remission rates (platelet count >30×10^9^/L and at least twofold increase from baseline); Complete 100×10^9^/L, partial 30−100×10^9^/L.Time to relapse and time to next therapy.Cumulative corticosteroid dose.Need for rescue therapies.Need for splenectomy.Socioeconomic costs.Patient-reported outcomes (quality of life, fatigue, impact of bleeding, care costs).

### Patients follow-up

Patients will be followed up until the end of the trial and for a minimum of 12 months. They will receive the usual follow-up according to clinical need and local policy. Laboratory and clinical data will be collected from routine appointments. In addition, patient-oriented outcomes and additional data will be recorded at diagnosis, 2, 4, 6 and 12 months using validated patient questionnaires. Patients are also offered consent to additional blood samples for translational research studies (time 0 and 2 months).

### Data collection

Hospital monitoring of platelet levels (FBC) is part of routine care for patients with ITP and these data will be collected and recorded on the CRF without requiring patients to come in for additional samples to be taken. These locally collected samples may be collected monthly (or less often) for patients believed to be in stable remission and weekly at lower or declining platelet levels. We expect this to allow us to calculate the time in remission and time to relapse with reasonable accuracy over the 12–24 months follow-up period. Other clinical and laboratory data needed for the trial endpoints will be collected from the medical and electronic records and recorded on the CRF. In addition, we will also ask the patients to complete questionnaires on fatigue, quality of life and bleeding scores at baseline, 2, 4, 6 and 12 months (table 1).

**Table 1 T1:** Time schedule of enrolment, interventions, assessments and visits

Procedures	V0	V1	V2 (two months)	V3 (four months)	V4 (six months)	V5 (12 months)	V6 12–24 months
	Screen	Baseline/randomisation to pathway 1 or 2	Follow-up	Follow-up	Follow-up	Follow-up	Data collection from sites
Eligibility assessment	x						
Randomisation		x					
Informed consent		x					
Demographics		x					
Medical history		x	x	x	x	x	
Physical examination		x					
Vital signs (incl height and weight)		x	x	x	x	x	
Pregnancy test	x						
Concomitant medications		x	x	x	x	x	
Standard practice bloods (includes blood sugar if applicable)	x	x	x	x	x	x	
Hepatitis B, C and HIV serology	x						
Immunoglobulins (blood)		x			x	x	
Extra blood samples (optional)		x	x				
Dispensing of trial drugs		x*					
Compliance			x				
QofL FACT-Th6, V.4	x	x	x	x	x	x	
QofL ICECAP V.2—A measure	x	x	x	x	x	x	
QofL SF-36V.2— Health Survey	x	x	x	x	x	x	
QofL FACIT-F, V.4, pg 3 (fatigue)	x	x	x	x	x	x	
QofL Thrombocytopenia costs questionnaire	x	x	x	x	x	x	
Data collection from sites on platelet count and treatment		x	x	x	x	x	x

*MMF and corticosteroid dispensing frequency can follow standard local practice.

MMF, mycophenolate mofetil; QofL, quality of life.

Patient-reported outcomes will be captured by the following questionnaires:SF36V.2 (Your health & well-being)—quality of life.FACIT-fatigue (V.4)—fatigue.FACT-Th6 (V.4)—bleeding.ICECAP-A V.2—quality of life.Health economic/resource use questionnaire—personal and social costs.

Additional optional research blood samples (requiring separate consent) will be sent at baseline and 2-month follow-up to the Bristol Biobank.

### Data management

Source documents produced for this trial will be kept in the patient’s hospital records and source data will be transcribed into trial-specific CRFs at the end of each patient visit. Data recording for this trial will be via a web-based system. This is a secure encrypted system accessed by an institutional password which complies with Data Protection Act standards. The database will be stored and regularly backed up on a Cardiff University Server. The CRFs will be coded with the study number and will not include patients’ names and addresses

### Patient and public involvement and engagement

During the trial development, a group of eight patients with ITP discussed the study design, burden of outcome measure completion to patients and the size of a potential placebo capsule which they reported could put them off getting involved in a trial. They reported that avoidance of relapse, early achievement of a stable platelet count, reduced overall corticosteroid dose and reduced hospital attendances are the most important goals for ITP management from their perspective.

We formed a patient advisory group with some of these patients and representatives from the ITP association that will advise the trial management group (TMG) throughout the study. They have commented on all patient-facing documentation and will be instrumental in disseminating the study findings to patient groups and the public.

## Statistics and data analysis

### Sample size calculation

There are no published clinical data available for MMF use first line in ITP as this is a novel approach. We have analysed local data on MMF used second line in ITP in 12 patients which shows an estimated median survival free from treatment failure of more than 10 months. We have data on 68 who experienced corticosteroids as a first-line treatment showing that 70% of them had experienced a treatment failure by 12 months and that the median survival free from treatment failure was 5.0 months (95% CI 3.2 to 6.8). Data for the 12 patients treated with MMF second-line therapy have shorter follow-up times, with only 5 patients having follow-up beyond 12 months. The Cox proportional hazards regression model demonstrates the 90% CI for the HR to be between 0.13 and 0.59, showing that our decision to power this on an estimate of a hazard of lower than 0.5 is potentially achievable.

Clinically a doubling in the time to remission was thought to be something that the patients would have welcomed. Less than that was not thought to be sufficient grounds for switching this treatment from second line to first line due to the potential for additional toxicity and immune suppression in those who may have remained in remission with corticosteroids alone.

The sample size of 120 (60 per group) with less than 5% loss to follow-up achieves 91.5% power to detect a doubling of the median time to treatment failure from 5 to 10 months if the patients are recruited at a steady rate or 10 per month for 12 months and all followed up until the last patients reaches 12 months follow-up.

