**Analysis:**

The sample size of 120 achieves a 91.5% power to detect a doubling of the median time to treatment failure from 5 to 10 months. This will be expressed as an HR with 95% CI, median time to event if more than 50% have had an event and illustrated with Kaplan-Meier curves. Cost-effectiveness will be based on the first 12 months from diagnosis.

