This trial proposal has received support and input from clinicians and patients nationally (UK ITP forum and ITP support association). To ensure objective and meaningful outcomes, it will be a multicentre RCT, aiming to recruit 120 patients (expecting 100 full datasets). Patients will be given up to 1 week of corticosteroid prior to randomisation to enable sufficient time to read information, discuss and ask questions with informed consent in an appropriate setting. Patients will receive the usual follow-up according to clinical need and local policy. Laboratory and clinical data will be collected from routine appointments. In addition, patient-oriented outcomes will be recorded at diagnosis, 2, 4, 6 and 12 months using validated patient questionnaires. Patients are also offered consent to additional blood samples for translational research studies (time 0 and 2 months).

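### The 91.5% power belongs to HR 0.5 under a constant hazard; on the protocol's own control figures a 5-to-10-month doubling of the median is a weaker effect, with power nearer 50%

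*Protocol article*

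**What the plan says.** The abstract (Analysis) and the section Sample size calculation make the same claim. In the latter, a trial of 60 patients per group, losing under 5%, is said to be one that "achieves 91.5% power to detect a doubling of the median time to treatment failure from 5 to 10 months". Recruitment is 10 per month for 12 months, with follow-up until the last patient reaches 12 months.

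The same section also gives a target on the hazard scale: "our decision to power this on an estimate of a hazard of lower than 0.5 is potentially achievable". It describes doubling as the least improvement that would justify moving MMF to first line.

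The control assumption comes from 68 patients given first-line corticosteroid. The section reports of these: "70% of them had experienced a treatment failure by 12 months and that the median survival free from treatment failure was 5.0 months". Its confidence interval for this median runs from 3.2 to 6.8 months. Elsewhere, the abstract's introduction puts sustained remission after corticosteroid at 20%, and the Rationale allows that 10%–30% might succeed on corticosteroid alone. The article names neither a survival distribution nor a significance level for the power calculation.

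**The concern.** A doubled median and a halved hazard are the same effect only when the hazard is constant. The section uses both descriptions as if they were interchangeable, yet the control figures beside them describe a curve that drops early and then flattens. On such a curve the two targets separate, and the quoted power belongs to the hazard ratio, not to the median.

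What is at stake is how the result is read. Doubling is the stated threshold for changing practice. A non-significant result could be taken as good evidence against a doubling of the median, on the strength of 91.5% power, when the chance of detecting that effect may have been much lower.

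**Working it through.** **Inputs.** 60 per arm, 1:1; accrual uniform over 12 months, so follow-up is uniform on 12–24 months; control median 5.0 months; 70% of controls failed by 12 months; MMF median 10 months or HR 0.5; loss below 5%. Assumed: two-sided 5%, consistent with the planned 95% CI.

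**Power formula (Schoenfeld).** Power = Φ(½·√d·|ln HR| − 1.96), where d is the expected number of events.

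**1. Reproducing the stated figure.** With exponential times, λ = 0.693/median, and the mean event probability over follow-up is 1 − (e^(−12λ) − e^(−24λ))/(12λ).
- Control: λ = 0.1386, probability 0.908. MMF: λ = 0.0693, probability 0.704.
- d = 60 × (0.908 + 0.704) = 96.7. Power = Φ(½ × 9.84 × 0.693 − 1.96) = 92.6%.
- With 5% fewer events (91.9): 91.3%. The stated 91.5% is therefore reproduced.

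**2. Does that curve fit the control data?** An exponential with median 5 has 1 − 0.5^(12/5) = 81% failed by 12 months, against 70% reported, and 0.5^(24/5) = 3.6% failure-free at 24 months, against about 20% in sustained remission. An exponential through 70% at 12 months has median 12 × 0.693/1.204 = 6.9 months, just above the upper limit of 6.8. The joint pattern suggests a falling hazard.

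**3. Curves through both control points, S(5) = 0.50 and S(12) = 0.30.** For a Weibull, shape = ln(1.204/0.693)/ln(12/5) = 0.63. Then S(10) = 0.342, and an MMF median of 10 months under proportional hazards is HR = 0.693/1.073 = 0.646. With 84.8 events, power = Φ(½ × 9.21 × 0.437 − 1.96) = 52%. Other shapes are handled in the same way:

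| Control curve | HR for median 10 | Events | Power (5% fewer events) | Power at HR 0.5 (5% fewer events) | MMF median at HR 0.5 |
|---|---|---|---|---|---|
| Weibull, shape 0.63 | 0.646 | 84.8 | 52% (50%) | 87% (85%) | 15.0 months |
| Piecewise exponential, change at 5 months | 0.655 | 87.3 | 51% (49%) | 88% (86%) | 14.5 months |
| Plateau, 24% long-term free | 0.626 | 78.1 | 54% (52%) | 84% (82%) | 22 months |

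Log-rank simulation on the Weibull curve (20,000 trials, no loss) gives 52% for median 10 and 87% for HR 0.5.

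**4. Range for a 10-month median.**
- Non-proportional versions (simulation): 46% for a Weibull control against an exponential MMF arm; 42% for the plateau curve with its time scale doubled.
- Setting the 70% figure aside and using only median 5.0 with a 20% plateau: 72% failed by 12 months, HR 0.596, 81 events, 65% power.

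The range is roughly 42–65%.

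**5. Sensitivity to the 12-month input.** A Weibull with median 5 and 75% failed by 12 months, in place of 70%, gives 74% power for median 10. An exponential fitted to the 70% figure alone (median 6.9, doubled) keeps 89%.

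**The case against.** Three points on the other side carry weight.

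- **The arithmetic is right.** A reader might infer a calculation error. There is none: 91.5% follows from the stated inputs under the conventional exponential assumption.
- **The protocol also names HR below 0.5 as its target.** The primary result will be an HR with a 95% CI. At HR 0.5 power stays above 80% on every curve tried. It would be wrong to conclude that the trial as a whole is a coin toss; that describes only a 10-month median on these control curves.
- **The control inputs are imprecise.** A rough binomial 95% CI for 70% of 68 is 0.70 ± 1.96 × √(0.7 × 0.3/68), or 59–81%, so the exponential's 81% is at its edge. A constant hazard with median 6.8 months, the upper limit of the CI, gives 70.6% failed by 12 months. The article does not say whether 70% is crude or Kaplan-Meier; a crude figure that counts censored patients as non-failures would understate failure and exaggerate the flattening. The data do not fit a 5-month exponential well, but they do not disprove a constant hazard.

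These limit the precision of the 50% figure. They do not remove the mismatch, because the 20% sustained remission is a separate figure pointing the same way, and the published sentence attaches the power to the medians.

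A reader might also see a contradiction between loss below 5% and the Rationale's "aiming to recruit 120 patients (expecting 100 full datasets"). The documents do not support that. A full dataset may include the questionnaires to 12 months, and the primary analysis keeps every randomised patient for as long as followed.

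**Conclusion.** The point holds in a limited form. The 91.5% is correct for HR 0.5 with exponential failure times, but it is published as the power for a median rising from 5 to 10 months. On the protocol's own control figures that is a weaker effect (HR about 0.60–0.66), with power of about 50%, plausibly 42–65% by curve shape. For HR 0.5 on curves through the two control points, power is about 82–86% with 5% loss, and the MMF median would be about 14.5–22 months, not 10.

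This rests on a two-sided 5% level, which the article does not state, and on two point estimates from 68 patients. The direction is well supported; the exact size is not. The design remains reasonable for the hazard-ratio target.

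**What to change.** In the abstract and in Sample size calculation:

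1. State the target as HR 0.5, with the significance level and the survival distribution assumed.
2. Give power for HR 0.5 under a declining control hazard (about 82–86% with 5% loss), and say that 91.5% applies to exponential times.
3. Remove the claim of 91.5% power for a 5-to-10-month doubling, or qualify it with the approximate range and the reason for its uncertainty.
4. Say whether the 70% is crude or Kaplan-Meier.
5. Add a clause in the Rationale explaining that the 100 full datasets are not the loss rate for the primary endpoint.

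The cost is text only and a less favourable stated power. No extra patients are needed.
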